## Abstract

**Background:**

Nonsuicidal self-injury (NSSI), defined as the deliberate, self-inflicted damage of body tissue without suicidal intent, is increasingly prevalent among adolescents and young adults and poses a major public health concern. Current treatments are often costly, difficult to access, and not tailored to the specific needs of young people. Mobile health (mHealth) interventions represent a promising avenue for scalable, accessible, and cost-effective support for NSSI, especially when combined with real-time assessments and personalized treatment strategies.

**Objective:**

This randomized controlled trial will evaluate the effectiveness of Kalmer, a brief app-based intervention for reducing NSSI and improving emotional well-being. The study has 2 aims: (1) to evaluate a newly developed app-based intervention for adolescents and young adults engaging in NSSI and (2) to assess predictors of treatment outcomes for this app-based intervention. We hypothesize that participants receiving a mobile app–based brief intervention specifically tailored to address NSSI will show a greater reduction in NSSI frequency at the end of treatment and at follow-up than participants receiving a nonspecific app-based intervention. In this paper, we present our study protocol.

**Methods:**

This 2-arm randomized controlled trial, lasting 6 weeks, will include 240 participants aged 14 to 24 years who engage in NSSI. The intervention app, Kalmer, was developed through iterative consultation with clinical and research experts and guided by survey results and evidence-based frameworks such as dialectical behavior therapy and cognitive behavioral therapy. The intervention will include 5 core components: distress tolerance, emotion regulation, mindfulness and self-compassion, interpersonal regulation, and problem-focused coping. The app will deliver multimedia-based ecological momentary interventions triggered by real-time ecological momentary assessments to tailor support to users’ current contexts and needs. Participants are randomized to receive either the Kalmer intervention or a psychoeducational control app. The primary outcome will be NSSI frequency, assessed through self-report at baseline, 6 weeks after intervention, and at 1-month and 3-month follow-ups.

**Results:**

Ethics approval was obtained in December 2022. As of January 2026, a total of 145 participants had consented to participate in the study and completed baseline assessments. Preliminary data show high app engagement and acceptability and positive user feedback regarding app usability and content. Recruitment is ongoing.

**Conclusions:**

This study will provide evidence on the effectiveness of a mobile app–based intervention for NSSI and will explore potential mechanisms of change, supporting the development of accessible digital mental health tools for adolescents and young adults.

**Trial Registration:**

International Standard Randomized Controlled Trial Number Registry ISRCTN63093907; https://www.isrctn.com/ISRCTN63093907

**International Registered Report Identifier (IRRID):**

DERR1-10.2196/86413

## Introduction

Nonsuicidal self-injury (NSSI) is the deliberate destruction of one’s own body tissue in the absence of suicidal intent and is a growing public health concern, particularly among adolescents and young adults [1,2]. NSSI imposes a substantial burden not only on individuals and their families but also on health care systems and society at large. Prevalence rates suggest that 17.2% of adolescents and 13.4% of young adults in community samples report at least one episode of NSSI, with rates reaching up to 58% in clinical adolescent populations [3,4]. NSSI is associated with potentially negative consequences, including impaired interpersonal, academic, and daily functioning, and is one of the strongest predictors of suicidal behavior [5]. In recognition of its severity, the World Health Organization has identified NSSI as one of the top 5 major health threats to adolescents, and it has been included in the *Diagnostic and Statistical Manual of Mental Disorders, Fifth Edition*, as a condition requiring further research.

NSSI often begins during early adolescence and is frequently associated with chronic psychosocial stress, peer rejection, or family-related neglect [6]. Individuals who engage in NSSI typically report greater psychological distress than their peers, regardless of clinical status [4]. In clinical settings, NSSI is commonly observed in the context of broader internalizing and externalizing conditions such as depression, borderline personality disorder (BPD), and eating disorders [7]. Although NSSI is primarily used to regulate negative emotions, it serves a range of functions, both intrapersonal (eg, to relieve distress) and interpersonal (eg, to communicate needs or influence relationships) [8]. According to the 4-factor model of NSSI, these functions can be either positively or negatively reinforced and often co-occur within the same individual [9].

Despite progress in understanding NSSI, significant gaps remain, particularly in the identification of effective, scalable interventions and the mechanisms underlying treatment response. Established treatments such as dialectical behavior therapy (DBT), cognitive behavioral therapy (CBT), and mentalization-based therapy have shown efficacy in reducing NSSI, especially among young adults with BPD traits, but are resource intensive and limited in accessibility [10-12]. Many adolescents and young adults with NSSI face substantial barriers to accessing care, including stigma, a lack of specialized clinicians, and reluctance to seek face-to-face treatment [13].

In this context, digital mental health interventions, particularly mobile apps, represent a promising avenue for improving access to care. Mobile apps can deliver evidence-based support in a self-guided, scalable, and cost-effective format [14]. Young people report high levels of interest in and engagement with digital tools for mental health. However, most app-based interventions currently available either do not specifically target NSSI or have limited empirical support [15]. Furthermore, very few studies have explored their utility in nonclinical populations, despite the growing prevalence of NSSI in these groups. Importantly, there is also limited knowledge regarding individual-level predictors of treatment response, which hinders the development of personalized digital interventions.

To address these gaps, we have developed Kalmer, a brief mobile app–based intervention designed specifically for adolescents and young adults who engage in NSSI. The app has been developed through a structured process that includes expert consultations and survey-based feedback, ensuring that the intervention is grounded in clinical and empirical knowledge. Kalmer integrates ecological momentary assessments (EMAs) to monitor users’ emotional states in real time and trigger tailored ecological momentary interventions (EMIs) delivered through multimedia formats (eg, video, audio, text, and image-based content).

This paper presents the protocol for a randomized controlled trial (RCT) to evaluate the feasibility, acceptability, and preliminary efficacy of the Kalmer intervention. The study will include both clinical and subclinical participants aged 14 to 24 years with a history of NSSI. The primary aim is to develop Kalmer and assess whether it reduces NSSI frequency. The secondary aim is to identify behavioral predictors of treatment response using self-report and real-time app data. This research has the potential to inform the development of accessible, personalized, and evidence-based digital interventions for young people who engage in self-injury.

## Methods

### Study Design and Intervention Arms

#### Overview

This study is a multicenter, double-blinded RCT evaluating the effectiveness of a brief mobile app–based intervention for NSSI in adolescents and young adults. The study was registered with the International Standard Randomized Controlled Trial Number registry. Participants are being randomized to either an NSSI-specific intervention app (intervention 1) or a nonspecific control app (intervention 2).

#### Intervention 1: NSSI-Specific Intervention App

##### Development and Design of Kalmer

The NSSI-specific intervention app, Kalmer, has been designed as a brief app-based program targeting NSSI in adolescents and young adults. It combines evidence-based components from CBT and DBT, with the aim of expanding users’ repertoire of coping strategies to improve well-being, distress tolerance (DT), autonomy, decision-making, problem-solving, sense of meaning, and effectiveness in social relationships.

The intervention content was developed through an iterative process involving both clinical and academic experts in NSSI, digital mental health, and adolescent psychopathology. Experts participated in structured meetings and completed targeted surveys to validate and prioritize the core therapeutic elements. This process led to the definition of 5 therapeutic domains that structured the intervention: distress tolerance (DT); mindfulness and self-compassion (M); interpersonal regulation (IR); and problem-focused coping (PC). A schematic representation of the EMA-EMI sequence is shown in Figure 1 (left panel).

**Figure 1 figure1:**
[figure not shown]
Screenshots of the Kalmer app. (A) Initial ecological momentary assessment (EMA), in this example rating the extent to which the participants feel distracted in the present moment. (B) Based on the EMA response, the app then delivers a tailored ecological momentary intervention (EMI) in a multimedia format, such as audio, video, or an infographic. (C) An EMA is used to collect feedback on the perceived usefulness of the exercise. (D) A screenshot of the main menu of the Kalmer app. T1: time point 1; T2: time point 2; T3: time point 3.

##### Ecological Momentary Assessments

EMAs were constructed to gather daily, real-time information on participants’ emotional states, perceived social support, NSSI behaviors, and coping strategies aligned with the 5 therapeutic domains. The assessments were derived from validated psychometric instruments, including the 15-item Five Facet Mindfulness Questionnaire [16,17], the 28-item Coping Orientation to Problems Experienced questionnaire [18,19], the 12-item Interpersonal Support Evaluation List [20,21], the Difficulties in ER Scale (DERS) [22,23], and the Inventory of Statements About Self-Injury (ISAS) [24].

Table 1 shows 2 types of EMAs that were implemented. On-demand EMAs were accessible at any time and provided participants with an immediate, tailored EMI upon completion. Scheduled EMAs were delivered daily at 6:00 PM, with a reminder at 7:00 PM, to ensure consistent engagement. The question sets varied slightly between the on-demand and the scheduled EMAs. Additional items regarding social media use were included in the scheduled EMAs, given their relevance in this age group and their established association with NSSI behaviors [25,26].

**Table 1 table1:** Scheduled and on-demand ecological momentary assessment (EMA) questions.

Component	On-demand EMA	Scheduled EMA
Emotion regulation	At this moment, to what extent do my emotions seem overwhelming to me?	At this moment, to what extent do my emotions seem overwhelming to me?
Interpersonal regulation I	During the day today, to what extent am I spending more time than usual on social media because I feel lonely and/or rejected?	At this moment, to what extent do I feel lonely and/or rejected?
Interpersonal regulation II	N/A^a^	During the day today, how many hours have I spent on social media?
Interpersonal regulation III	N/A	During the day today, to what extent have I spent more time than usual on social media because I have felt lonely and/or rejected?
Mindfulness	At this moment, to what extent do I feel that my mind is wandering?	At this moment, to what extent do I feel that my mind is wandering?
Problem-focused coping	At this moment, to what extent do I feel able to cope with my problems?	At this moment, to what extent do I feel able to cope with my problems?
Distress tolerance	At this moment, to what extent do I think about harming myself?	At this moment, to what extent do I think about harming myself?

^a^N/A: not applicable.

##### Ecological Momentary Interventions

EMAs dynamically trigger EMIs tailored to participants’ real-time needs. EMIs are delivered through multimedia formats, including videos, images, infographics, audio clips, and external links. Each EMI module features a short video with psychoeducation, examples, and simulated testimonies, followed by exercises designed for real-world application.

The first week of app use includes daily introductory videos presenting each therapeutic component and encouraging adherence. Both scheduled and on-demand EMAs and EMIs will be available throughout the intervention period.

The DT domain was prioritized because of its strong association with NSSI behaviors [27]. DT-focused EMIs aimed to help users withstand intense emotional states without resorting to NSSI, emphasizing skills for tolerating, but not necessarily reducing, the intensity of distress until it subsides.

The ER component focused on helping participants understand and modulate strong positive and negative emotions, as emotional cascades are a known trigger for self-injury [27]. The mindfulness and self-compassion domain equipped users with skills to remain present and attuned to their emotions, thereby enhancing the application of other coping strategies.

The interpersonal regulation and problem-focused coping domains address relational difficulties and life challenges that are particularly salient during adolescence and young adulthood [28]. Strategies within these domains aim to mitigate feelings of rejection and abandonment, both of which are linked to NSSI [6,29].

##### Multimedia Content and Prioritization

A total of 32 EMI videos, 50 images, 42 infographics, 8 audio files, and 6 YouTube links were created to explain therapeutic strategies, provide psychoeducation, and encourage skill application. EMIs were prioritized based on expert judgment: when the user reaches the specific scores detailed in Table 2, an EMI will be activated to offer the intervention objects linked with the score and its component. If multiple components warranted intervention, the app delivered the EMI corresponding to the most maladaptive state at that moment. The decision rules for EMI selection and prioritization are detailed in Table 2.

**Table 2 table2:** Ecological momentary intervention (EMI) component order.

EMA^a^ score	EMI component
DT^b^ between 8 and 10	DT content related to doing something else to avoid self-injury, as “STOP^c^,” “opposite action,” and “distraction” techniques, but focused on dealing with NSSI^d^ behaviors
DT between 6 and 7	DT content related to activities or strategies that can be used to delay NSSI behaviors
ER^e^ between 8 and 10	ER content related to doing something else or different, as “STOP,” “opposite action,” and “distraction” techniques
IR^f^ between 8 and 10	IR content related to not acting impulsively, contact with support network and emotion management of difficult situations.
M^g^ between 5 and 10	M content related to practicing mindfulness with different strategies.
ER between 6 and 7	ER content related to reevaluation and relaxation.
IR between 6 and 7	IR content related to how to connect with others
DT between 4 and 5	DT content related to things to do to protect yourself in the event of NSSI behaviors appearing, such as safety plans.
PC^h^ between 0-3	PC content related to the steps to solve problems and to make decisions.
ER between 4 and 5	ER content related to normalizing the emotions felt in the moment.
IR between 4 and 5	IR content related to remind the user to connect with people and that is not alone.
PC between 4 and 6	PC content related to short reminders of how to deal with problems.
SM^i^ between 7 and 10	SM content to explain how social media do not help with rejection feelings.

^a^EMA: ecological momentary assessment.

^b^DT: distress tolerance.

^c^STOP: stop, take a breath, observe, and proceed mindfully.

^d^NSSI: nonsuicidal self-injury.

^e^ER: emotion regulation.

^f^IR: interpersonal regulation.

^g^M: mindfulness.

^h^PC: problem-focused coping.

^i^SM: social media.

The app also featured 2 content libraries. The “Review My Contents” section served as a repository of all previously received EMIs, allowing users to review and practice the strategies at any time. The “General Contents” section provided crisis hotline numbers and links to reputable websites related to self-injury and mental health. Figure 1D shows the 3 principal options displayed in the app: “Answer now,” “Review my content,” and “General content.”

##### Youth Advisory Board

A youth advisory board composed of 9 young adults with lived experience of NSSI provided systematic feedback on the app’s functionality, design, and overall user experience. Their perspectives informed the development of the final version of the Kalmer app.

#### Intervention 2: Nonspecific Control App

Participants assigned to intervention 2 group use the same Kalmer app interface, which adheres to the same EMA schedule as those in intervention 1. However, this version delivers static, nonpersonalized content that is not tailored to individual EMA responses. Specifically, the app comprises 2 psychoeducational modules: (1) an introductory module outlining the app-based intervention and providing general information on NSSI and (2) a module focused on emotional well-being, healthy lifestyle behaviors, and strategies for managing anxiety.

For both intervention 1 and intervention 2, app use metrics (eg, session completion rates and time spent within the app) are being collected continuously. In either condition, any participant reporting recurrent self-injury or heightened clinical risk will prompt the research team to notify the participants’ clinical care team to initiate an appropriate safety protocol. Additionally, both versions of the app include a “General contents” section containing the national suicidal behavior hotline number and links to validated online resources pertaining to self-injury and mental health.

### Participants, Eligibility Criteria, and Recruitment

Recruitment is ongoing, and we aim to recruit a total of 240 participants aged 14 to 24 years. As shown in Table 3, all participants will have engaged in at least 5 episodes of NSSI in the past year and will have access to a smartphone. They must also provide informed consent; parental consent is required for minors. Exclusion criteria for all participants include a current psychiatric crisis or inability to complete study procedures.

**Table 3 table3:** Inclusion and exclusion criteria for the study groups.

Inclusion and exclusion criteria	Study groups	
	Clinical	Subclinical
Aged 14-24 y	✓	✓
Providing informed consent online	✓	✓
Owning a smartphone	✓	✓
Having engaged in NSSI^a^ on ≥5 different days in the last 12 months	✓	✓
Co-occurring with any other diagnosis	✓	
Currently receiving psychological or psychiatric treatment	✓	
Absence of important clinical instability	✓	✓

^a^NSSI: nonsuicidal self-injury.

Participants with NSSI are being recruited from clinical sites (ie, clinical group, n=120) and from the community (ie, subclinical group, n=120). Participants categorized as clinical are receiving treatment from one of the mental health service sites involved in this study, whereas subclinical participants are not receiving treatment from a public mental health unit. Recruitment is being carried out through multiple channels including clinics, schools, social media, and mental health organizations. A dedicated study website provides information, facilitates consent, and guides participants through the screening and assessment process.

### Screening, Baseline, and Follow-Up Assessments

Interested individuals are being contacted by the study’s research assistant and invited to attend a screening interview, during which they receive detailed information about the study, undergo an eligibility assessment for participation, and provide informed consent in electronic or paper form. For participants younger than 18 years, parental consent is also required. Upon consent, participants complete the online assessment protocol consisting of sociodemographic information and validated self-report questionnaires. Participants are invited to complete online questionnaires at multiple time points throughout the study to assess primary and secondary outcomes and momentary data during the app-based intervention. Figure 2 provides an overview of the instruments administered at each assessment point (T0-T3), including baseline, treatment start, postintervention, and 3-month follow-up evaluations.

**Figure 2 figure2:**
[figure not shown]
Schedule of self-report measures administered across study time points (T0-T3). BEAQ: Brief Experiential Avoidance Questionnaire; BSL-23: Borderline Symptom List–23; DASS-21: Depression Anxiety Stress Scales; DERS-18: brief version of the Difficulties in Emotion Regulation Scale; DoM: Delusion of Me; DTS: Dialectical Thinking Scale; ISAS: Inventory of Statements About Self-Injury; MPSS: Multidimensional Scale of Perceived Social Support; NSSI: nonsuicidal self-injury; NSSIDS: nonsuicidal self-injury disorder scale; PANAS: Positive and Negative Affect Schedule; PHI: Pemberton Happiness Index; SUS: System Usability Scale.

### Description of Measures

#### Screening Interview

Questionnaires at the baseline interview assessment include the validated Spanish version of the Patient Health Questionnaire-9 [30-32]. Selected items from the Columbia-Suicide Severity Rating Scale [33] are also used. Finally, the clinician-rated severity of NSSI, a 5-point scale developed to assess the severity of NSSI behaviors experienced by an individual in the past year, is being completed [34].

#### Primary Outcome

The primary outcome is the frequency of NSSI behaviors, assessed using the ISAS [24] at the predefined study time points. At baseline (T0), the ISAS assesses the lifetime frequency and functions of NSSI behaviors [24]. At follow-up assessments, a modified version of ISAS is used to inquire about NSSI behavior in the last month. The Spanish version of the ISAS is used in this study, demonstrating strong internal consistency for both the interpersonal and intrapersonal subscales (Cronbach α=0.87 and 0.90, respectively) [35].

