### Statistical Analysis

Primary analyses will be conducted using linear mixed-effects models to evaluate the impact of the intervention on both momentary and self-report outcomes. Time (T0, T1, T2, and T3) will be included as a within-subject factor, while intervention (intervention 1 vs intervention 2) and group (clinical vs subclinical) will be modeled as between-subject factors. Random intercepts for participants and random slopes for time will be specified. Secondary analyses will explore potential moderators and mediators of treatment response, including app engagement, baseline severity, and demographic variables. Missing data will be addressed using maximum likelihood estimation under the assumption that data are missing at random.

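### The primary outcome counts lifetime episodes at T0 and last-month episodes afterwards, yet T0 is a level of the same time factor, so change from T0 is not a reduction in NSSI frequency

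*Protocol article*

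**What the plan says.** All references are to the protocol article.

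- **Primary Outcome section.** The primary outcome is NSSI frequency on the ISAS. The recall window changes between visits: "At baseline (T0), the ISAS assesses the lifetime frequency and functions of NSSI behaviors", and "At follow-up assessments, a modified version of ISAS is used to inquire about NSSI behavior in the last month".
- **Statistical Analysis section.** "Primary analyses will be conducted using linear mixed-effects models to evaluate the impact of the intervention on both momentary and self-report outcomes". For the time variable, "Time (T0, T1, T2, and T3) will be included as a within-subject factor", and "Random intercepts for participants and random slopes for time will be specified". No offset, rate conversion or covariate role for T0 is stated.
- **Abstract, Objective.** The hypothesis is that participants given the NSSI-specific app "will show a greater reduction in NSSI frequency at the end of treatment and at follow-up", compared with those given the nonspecific app.
- **Visit schedule.** The Abstract (Methods) has the outcome "assessed through self-report at baseline, 6 weeks after intervention, and at 1-month and 3-month follow-ups", so every visit after baseline follows the intervention. The section on screening, baseline and follow-up describes T0 to T3 as "including baseline, treatment start, postintervention, and 3-month follow-up evaluations", which puts one further visit at the start of treatment. Figure 2, which holds the schedule of measures, is not shown.

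**The concern.** A reduction needs a before-value and an after-value on the same scale. Here the before-value accumulates over a lifetime and the after-value over one month. Two consequences follow if the model is fitted as described.

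First, the time effect from T0 to any later visit is driven largely by the change of window. It would look like improvement in both arms even if nobody changed. The Ethical Considerations section makes the later offer of the app to controls depend on the study showing a significant reduction in NSSI frequency. It does not say which contrast decides this, and a within-arm fall from T0 would not be evidence of one.

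Second, lifetime totals are likely to vary far more between participants than one-month counts. Any arm contrast that subtracts T0 carries that extra variance.

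**Working it through.** **1. One participant with no change.** Suppose one episode a month for the 12 months before enrolment, none earlier, and one a month afterwards. The T0 value is 12 and each follow-up value is 1. The apparent change is 1 − 12 = −11, although behaviour is constant.

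**2. Is the arm contrast biased?** No. Randomisation gives the lifetime count the same expectation in both arms. In the difference between arms of (follow-up − T0), the T0 terms cancel in expectation and the treatment effect on the last-month count remains. The problem is precision and modelling of the T0 level.

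**3. Inputs for the size.**
- Evaluable per arm: 120 × (1 − 0.20) = 96, from the Sample Size Calculation section.
- Effect: d = 2f = 2 × 0.27 = 0.54 last-month SDs. This is an assumption. The stated 100 per group is reproduced by an F test on four cells (arm by clinical/subclinical, 3 numerator df): noncentrality 0.27² × 200 = 14.58, power 0.903 at N = 200. Read as a two-arm F test, f = 0.27 needs only 148 in total. The article does not say that f is the arm contrast.
- Correlation ρ between T0 and follow-up counts: not given, taken as 0.3.
- Ratio k = SD(lifetime) / SD(last month): not given, taken from 1 to 5.

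**4. Formulas**, in units of the last-month SD:
- Change from T0: V = k² + 1 − 2ρk
- Last-month count adjusted for baseline: V = 1 − ρ²
- SE = √(2V/96); power ≈ Φ(0.54/SE − 1.96)

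| Contrast | V | SE | Power |
|---|---|---|---|
| Change, k = 1 (matched window) | 1.40 | 0.171 | 88.5% |
| Change, k = 1.5 | 2.35 | 0.221 | 68.5% |
| Change, k = 2 | 3.80 | 0.281 | 48% |
| Change, k = 3 | 8.20 | 0.413 | 26% |
| Change, k = 5 | 23.0 | 0.692 | 12% |
| Last-month count alone | 1.00 | 0.144 | 96% |
| Last-month count, baseline-adjusted | 0.91 | 0.138 | 97.5% |

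Part of the gap would exist with a matched window too: 88.5% against 97.5% at k = 1. The rest is due to k.

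**5. Sensitivity to ρ.** With 100 per arm and ρ from 0.3 to 0.7, power of the change contrast is 50–73% at k = 2, 27–35% at k = 3 and 12–14% at k = 5. For k above 2 the change is noisier than the follow-up count alone even at ρ = 1, because V is then (k − 1)², which exceeds 1.

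**6. A four-visit model.** A simulation used 100 per arm, ρ = 0.5 and 4,000 runs, with a random intercept, one residual variance and no random slope. The omnibus arm-by-time test had power 98.7%, 69%, 42% and 22% at k = 1, 2, 3 and 5. Its type I error was about 5%, 7%, 9% and 10%. The mean contrast stayed at about 0.54 throughout, and an arm comparison at a single last-month visit kept about 97% power. This is simpler than the planned model, which has random slopes.

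**The case against.** The case on the other side has five parts.

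- **The primary question can still be answered.** A reader might infer that the planned analysis cannot answer it. The documents do not support that. Follow-up ISAS assessments share the last-month window, randomisation protects the arm contrast from bias, and arm differences at follow-up can be taken from the same fitted model. This stands.
- **Not every time effect is an artefact.** Only contrasts that involve T0 mix windows. This stands.
- **Very low power is not shown.** It depends on k and ρ, which the documents do not give. If each participant had a steady rate, the 12-month eligibility window alone would put k near 12, but month-to-month scatter would lower it. At k = 1.5 or 2 the loss is real but moderate. The figures are illustrations, and they describe a two-point change score rather than the planned model.
- **The residual structure is not stated.** The article does not commit to one residual variance across visits, and random slopes let the variance differ over time. A model with a free covariance matrix and equal baseline means in both arms would use T0 much as a covariate does. That detail may sit in the SAP, so the simulated type I error is not a property of the plan.
- **A matched baseline may exist.** If T1 is treatment start and a last-month ISAS is given then, there is one. The article does not say so, its Abstract points the other way, and T0 would still be a level of the time factor.

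None of this removes the core point: as written, the baseline level of the primary outcome is a different quantity from the later levels, and no conversion is given.

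**Conclusion.** The point holds in limited form. On the face of the Primary Outcome and Statistical Analysis sections, change from T0 mixes a lifetime count with a last-month count and cannot be read as a reduction in NSSI frequency. The arm-by-time contrast is unbiased but imprecise where it involves T0, and the T0 level is mis-modelled. Comparisons among last-month assessments are sound as far as the window is concerned.

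The loss of precision is conditional on the assumed 0.54 SD effect, 96 per arm, correlation 0.3 and, above all, the SD ratio. The plan needs correcting whatever that ratio is, because the interpretive fault does not depend on it.

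**What to change.** 1. Remove the lifetime T0 count from the response vector. Compare arms on last-month ISAS counts at the post-baseline visits, with log(1+lifetime ISAS) as a baseline covariate. The article has T0 ISAS measuring lifetime frequency, so the covariate should be available for everyone enrolled. The cost is a change of analysis wording.
2. Add the 12-month NSSI count as a second covariate only if it was recorded as a number. The eligibility section gives only a threshold of at least 5, worded as episodes in the text and as different days in Table 3.
3. Reconcile the two descriptions of the visit schedule and state whether T1 is treatment start. If a last-month ISAS is collected before treatment, use it as the baseline value and keep that visit out of the post-treatment comparison.
4. Otherwise, add the existing last-month form at T0 for participants still to be enrolled, as a supplementary baseline. As of January 2026, 145 of 240 had completed baseline, so at most 95 could supply it.

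The downside is that, without a last-month ISAS at treatment start, a matched baseline stays missing for those already enrolled. The main analysis should therefore rest on step 1, which does not need one.
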